## Abstract

**Background::**

Hundreds of youth psychotherapy randomized trials have generated scores of helpful empirically supported treatments (ESTs). However, the standardized structure of many ESTs and their focus on a single disorder or homogeneous cluster of problems may not be ideal for clinically referred youths who have comorbidity and whose treatment needs may shift from week to week. This concern has prompted development of flexible transdiagnostic, modular youth psychotherapies. One of these, designed for efficient training and implementation, is FIRST-a transdiagnostic intervention built on five empirically supported principles of change (i.e., feeling calm, increasing motivation, repairing thoughts, solving problems, and trying the opposite) and targeting common internalizing and externalizing youth mental health disorders and problems. FIRST has shown promise in improving youth mental health in three open trials. Now, in a more rigorous test, we seek to (1) conduct a randomized controlled trial comparing FIRST to usual care in real-world clinical practice settings; (2) examine a promising candidate mediator of change-regulation of negative emotions; and (3) explore variables that may influence clinicians’ treatment implementation.

**Methods::**

This is an assessor-naïve randomized controlled effectiveness trial in youth outpatient community clinics in New England and Texas. Using double randomization, clinic-employed clinicians and treatment-referred youths (7–15 years old) are independently randomly allocated (1:1) to FIRST or usual care. We aim to recruit 212 youth participants, all referred through normal community pathways, with elevated symptoms of anxiety, depression, conduct problems, or post-traumatic stress. This study will test the effectiveness of FIRST compared to usual care on mental health outcomes, examine whether those outcomes are mediated by regulation of negative emotions, and explore clinician factors that may be associated with FIRST implementation and outcomes. Session recordings are coded to assess treatment fidelity.

**Discussion::**

This study will evaluate the effectiveness of FIRST in youth community mental health settings, relative to the care usually provided in those settings. If FIRST is found to be effective, it could offer an efficient and practical method to increase use of empirically supported treatment principles in real-world practice contexts.

**Trial registration::**

NIH Clinical Trials Registry, NCT04725721. Registered 27 January 2021, https://clinicaltrials.gov/ct2/show/study/NCT04725721

## Introduction

Research across five decades has produced more than 500 published randomized controlled trials (RCTs) of youth psychotherapies-accompanied by scores of manual-guided protocols-many of which have been shown to effectively improve youths’ clinical outcomes and functioning and are thus deemed empirically supported treatments (ESTs). A meta-analysis of youth ESTs spanning more than three decades found a mean post-treatment effect size of 0.726 [1], indicating a medium-to-large effect [2].

However, when ESTs are tested in real world clinical practice settings against usual care (UC; i.e., everyday practices commonly employed in clinical settings) the overall effect size is much smaller (0.295) [3, 4]. This steep drop-off in effectiveness when ESTs are moved from laboratory to real world-termed the implementation cliff [5]-as well as evidence of limited uptake by community providers [6] suggests that some ESTs may need adjustments in design, delivery, and implementation to boost their effects in typical practice contexts. Many ESTs are lengthy, linear (i.e., using a relatively standardized sequence of sessions), and target only a single disorder or problem (or a cluster of related problems). While these approaches are efficacious and highly useful in many ways (e.g., treatment fidelity, replication of research), they pose at least five challenges to effective implementation in everyday clinical care.

First, clinically referred youths often present with multiple problems or comorbidities, yet most ESTs for youths focus on a single disorder or a small family of related problems [7]. Additionally, clinician caseloads span a wide range of problem areas, making learning one EST protocol-let alone several-highly inefficient [8]. Second, training clinicians to deliver one EST for one disorder can take several days, and therefore many separate trainings (which would be required for training in multiple EST protocols) would be needed to address most clinicians’ complex caseloads [9]. Third, most youth ESTs have a standardized linear design with a prescribed series of skills delivered in a relatively fixed order of sessions. This progression may not work well in everyday practice, where youths’ most pressing problems may change from week to week, requiring treatments that flexibly shift to address such fluctuations. Fourth, the typical recommended number of sessions for youth ESTs exceeds the average number attended by youth treated in community settings. Although the average EST includes 16 sessions spanning 16 weeks [1], most youths in outpatient care attend fewer than 8 sessions [10–12]. Accordingly, there is a need for more efficient treatments that maximize therapeutic benefits before attendance wanes. Fifth, although youth ESTs have been shown to effectively reduce youths’ mental health symptoms, little is known about the mechanisms underlying these effects [13]. Identifying such mechanisms could lead to a sea change in our understanding of how ESTs work, and what the active ingredients are, informing steps to make treatments more efficient and potentially more effective.

### Innovation

Efforts to address these barriers have prompted innovative approaches to youth psychotherapy treatment design, delivery, and implementation to match the real-world practice contexts. This has included the development of multi-diagnostic, modular treatments, such as the *Modular Approach to Therapy for Children with Anxiety, Depression, Trauma, and Conduct* (MATCH) [14]. MATCH offers clinicians a menu of 33 modules comprising core procedures from effective ESTs for various youth mental health concerns. Modules are grouped within the diagnostic categories for which they are used (e.g., exposure for anxiety, problem solving for depression). MATCH has shown significant effects relative to outpatient UC in two randomized controlled effectiveness trials (RCETs) [15, 16]. Other studies, however, have highlighted concerns about the lengthy (5–6 days) and costly training required, and findings have suggested that MATCH may be difficult to deliver effectively without a high level of implementation support (e.g., individual consultation) that is likely unsustainable in everyday clinical practice [17–19].

In response to these implementation challenges, we sought to develop a more efficient treatment for youths by drawing on empirically supported principles of change (ESPCs) [20–25] that can be applied across a range of disorders and problems. Our approach, *Principle-Guided Psychotherapy for Children and Adolescents: The FIRST Program* (hereafter FIRST) is a principle-guided, transdiagnostic treatment for youths [26], developed to address the aforementioned barriers to the delivery of ESTs in routine practice settings. The potential value of leveraging ESPCs has been articulated by members of the Society of Clinical Psychology EST Task Force [25] and others [e.g., 20, 21, 23, 24]. In short, although learning specific treatment techniques and procedures may be useful for clinicians, knowing *why* they are using these techniques (e.g., what kind of change process is needed to produce symptom reduction) may prove even more beneficial. Knowledge of ESPCs may be particularly important for community-based clinicians for whom EST approaches may be new [20–25, 27], or may represent a divergence from their usual clinical practice [23]. This rationale undergirds FIRST, which is based on five ESPCs supported by decades of research [28].

### Description of FIRST

The five core elements of FIRST are as follows:

**F**eeling Calm (calming, relaxation, emotion regulation),**I**ncreasing Motivation (incentivizing behavior change, e.g., via attention, praise, or rewards),**R**epairing Thoughts (cognitive reappraisal),**S**olving Problems (systematic steps of problem solving), and**T**rying the Opposite (practicing positive opposites that lead to corrective experiences, e.g., behavioral activation for depression, exposure for anxious avoidance).

Each principle can be flexibly and efficiently applied to the treatment of problems spanning depression, anxiety, obsessive-compulsive disorder, post-traumatic stress, and conduct problems among youth ages 7 to 15. FIRST was designed with input from experienced community clinicians and feedback from independent treatment developers and researchers [29].

FIRST has been tested in three open trials using low-cost training and clinician support. In the initial trial, Weisz and colleagues [29] tested FIRST in two community outpatient clinics with 24 community-referred youths. Treated youths had an average of 2.21 K-SADS diagnoses before receiving FIRST. At the end of treatment, 81*%* no longer met criteria for their primary diagnosis. Two subsequent open trials were conducted by Cho and colleagues [8] in an outpatient university training clinic with treatment duration limited to six sessions. In the first of these trials, FIRST was delivered to 22 youths ages 7 to 17. In the second, FIRST was delivered to 26 youths ages 11 to 17. In both trials, youths demonstrated improvements on youth- and caregiver-reported functional top problems and clinical symptom severity from session-to-session, as well as from pre-to-post on measures of both internalizing and externalizing symptoms. In all three trials, FIRST showed evidence of acceptability and feasibility [8, 29].

Building upon this initially promising evidence, our objective is to rigorously examine the effectiveness of FIRST in real-world clinical practice settings. Specifically, an RCET is being conducted to test FIRST relative to UC among ethnically and socioeconomically diverse youths (ages 7–15) who are referred through typical community channels, with treatment delivered by community clinicians (not research employees) in service clinics. These data are needed to determine whether FIRST can enhance youth outcomes in everyday practice when compared to usual care. In addition, the study will examine the role of a promising candidate mediator of change-the regulation of negative emotions-as an initial step in the search for a mechanism of change; the study will also explore implementation variables that are theorized to influence the adoption and effective use of ESTs in community settings.

## Methods

### Aims

The aims and specific research questions of the current trial are as follows:

To evaluate the effectiveness of FIRST compared to UC in community mental health clinics.
Does FIRST produce faster improvements (i.e., steeper slopes), compared to UC, on measures of internalizing, externalizing, total, and functional top problems during treatment and longer-term through 18 months?Does FIRST produce greater reductions, compared to UC, in total number of mental health diagnoses from pre- to post-treatment?To test a transdiagnostic candidate mechanism of change: regulation of negative emotions.
Does FIRST lead to faster improvements in regulation of negative emotions relative to UC?Does improved regulation of negative emotions predict faster improvements in youth clinical outcomes?Does improved regulation of negative emotions mediate the effects of condition (FIRST vs. UC) on youth clinical outcomes?To explore implementation variables specific to clinicians.
Do clinician characteristics (e.g., EST knowledge, attitudes, and intentions; perceived organizational climate) predict implementation fidelity, as assessed through observational coding of therapy sessions?Do clinician characteristics (e.g., EST knowledge, attitudes, and intentions; perceived organizational climate) moderate differences in implementation of EST practices between FIRST and UC, including adherence and competence in the delivery of ESTs?

### Design

This study is a multi-site RCET evaluating FIRST compared to UC in community outpatient clinics. The design employs single-masked evaluation on all measures (i.e., assessors are naïve to youths’ treatment condition). Allocation to treatment conditions entails masked, sequential, blocked double-randomization (i.e., of both clinicians and youths) within clinic using a computerized, sequential-block approach custom-built for the study with a 1:1 ratio (more details below). The concealment of allocation (until the time of condition assignment and beyond) is ensured primarily by restricting access to the randomization information via password-protected files and secure servers/logins (no one other than the project directors have access to randomization information). The random allocation programs were designed so that it is impossible to know the condition to which future participants will be assigned, even for the person performing the randomization. This concealment is further supported through masking of research staff through all phases of the study and by practices meant to eliminate risk for disclosure of allocation (e.g., study protocols are paper-free, so as not to conceal allocation using methods like envelopes, which could be held up to the light or opened and resealed).

All clinicians working at participating clinics (and new clinicians starting at the clinics during the study) are invited to participate and provide written informed consent. Upon enrolling, clinicians are randomly allocated to 1 of 2 conditions: the FIRST condition (i.e., to receive training and other implementation supports in FIRST; see “Intervention Condition: FIRST”) or the UC condition (i.e., to continue providing the treatment they ordinarily provide and believe to be effective; see “Control Condition: Usual Care”). Youth participants who seek treatment via typical referral processes at partner clinics are invited to participate in the study and screened for eligibility by study staff prior to obtaining informed consent from caregivers and assent from participating youths. Youths are then randomly allocated to condition (FIRST vs. UC). To avoid obstructing youths’ access to appropriate care, and to guard against the possibility of important condition differences emerging by chance, a few stratifications and constraints are employed. Random allocation is programed to achieve, approximately, (a) a balance of clinicians’ language fluency (English-only vs. Spanish-bilingual) and education level (doctoral vs. non-doctoral) across conditions; (b) a balance of youth age (younger [7–11] vs. older [12–15]) across conditions; and (c) a ~ 1:1 allocation ratio within each clinical site, for both clinicians and youths.

### Study Setting

This study is being conducted in outpatient mental health clinics serving youths in New England and Texas. These clinics have partnered with the research study team and are deemed “clinic partners.”

## Participants

### Youths and Caregivers

Youth participants include youths (ages 7–15 at the time of caregiver consent) and their caregivers (used to refer to parents or legal guardians who may or may not be parents) who are seeking mental health treatment at a clinic partner site.

#### Inclusion Criteria.

Youths are eligible to participate if:

They are newly referred for treatment at a partner clinic;They are between 7.0 and 15.9 years of age on the date of caregiver consent;They have at least one scale on the Child Behavior Checklist (CBCL) [30] that is clinically elevated (borderline or clinical range) for symptoms of anxiety, depression, conduct problems, or posttraumatic stress per caregiver report; and,They are fluent in English and their caregiver is fluent in English or Spanish.

#### Exclusion Criteria.

Youths are ineligible to participate if:

They have current suicide risk (i.e., active suicidal ideation with a plan, or a history of suicide attempt or hospitalization for suicide risk within the last 3 months); or,They have a diagnosis of an eating disorder, schizophrenia spectrum disorder, Autism Spectrum Disorder or intellectual disability requiring special class placement in school; or,They are referred for the treatment of ADHD specifically and exclusively to address inattentiveness and/or hyperactivity-impulsivity (youths with ADHD symptoms that have elevations in the areas of anxiety, depression, conduct problems, or stress problems on the CBCL are eligible).

Partner clinics identify potential participants during their standard initial intake assessment based on age (7–15) and disqualifying criteria (e.g., suicidality; defined above). Families considered potentially eligible are asked, following a scripted invitation, if the research team may contact the family with study information. If the caregiver gives permission, the research team contacts the family via phone to assess eligibility and provide information about the study. For families who agree to participate, caregivers provide written informed consent and youths provide written assent digitally. To provide fair compensation to families for their time and to incentivize participation and retention, youth and caregivers are compensated for their time completing study measures.

Participants can request to end participation in the study at any time. If participants experience increased risk of suicidal or homicidal behaviors during their participation, and partner clinics and clinicians determine a higher level of care is needed, research participation may be ended to ensure access to an appropriate level of care. Adverse events that are caused by the study are reported as “New Reportable Information” to the IRB. Following IRB review, the study team devises a plan to prevent future adverse events of the same nature.

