### Sample Size and Power

The target sample size is *N=212* youths. We used Optimal Design [59] to determine power for the main treatment effects, specifically comparing the rate of change for FIRST vs. UC. Assuming at least 24 providers, an ICC of 0.02 (based on prior RCETs), 5 of 6 repeated measures (quarterly schedule, anticipating some missing data), and standard thresholds for significance (α = 0.05), we determined that a minimum sample of *N*= 180 youth participants was required to achieve adequate power (1-β = 0.80) to detect an effect size of 0.50 (based on prior RCETs [15, 16] and a meta-analysis of youth ESTs [1]). Further, we anticipate an attrition/data loss rate of 15% will occur between allocation and analyses. Thus, a target sample size of *N*= 212 youths will ensure adequate power for the primary analyses (Aim 1).

Monte Carlo simulations were conducted in R using the simsem package [60] to estimate power for the Aim 2 mediation analyses. These simulations revealed that 180 participants will provide sufficient power to detect whether FIRST can produce a 0.36-*SD* change in the slope of the CBCL/YSR symptom improvement through the indirect effect of change in negative affect regulation.

Analyses of variables that may be associated with EST implementation (Aim 3) are considered exploratory and therefore were not designed to be adequately powered. Further, available power will vary across models. Nonetheless, power for these models was simulated using the simr package in R [61] which found a sample size of 180 to be adequate to detect a standardized regression coefficient as low as 0.25 for clinician-level predictors/moderators of outcomes within the FIRST condition (anticipating ~ 90 youths across 12–20 FIRST clinicians).

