### Planned Analyses

Prior to analysis, univariate, bivariate, distributional, and missing data characteristics of the data will be examined, and subsequent models will be adjusted (e.g., robust estimators, generalized models, non-parametric approaches) to ensure data-analytic assumptions are met. Baseline data from youths, caregivers, and clinicians will be compared across conditions, and any significant (*p*< .05) differences that emerge will be considered as covariates or moderators in subsequent analyses. Medication use, gender, and race/ethnicity may be examined as covariates and moderators in all outcome models to assess the robustness of effects. Missing data will be accommodated using full information maximum likelihood estimation or multiple imputation. Due to the low risk nature of this intervention, there will be no interim analyses; all data analyses will be conducted when data collection is complete.

### Aim 1

The effectiveness of FIRST compared to UC will be assessed using longitudinal multilevel models estimated with repeated measures at level 1 (5 +observations; random effects) nested within participants at level 2 *(N=* 180, random effects) nested within clinicians at level 3 *(N=* 24; random effects). Clinics will be modeled via dummy-coded fixed effects at level 3 and time will be modeled as linear or log-linear days since baseline. The effectiveness of FIRST vs. UC will be tested via the contrast term for the slopes of change in each condition. A significant (*p*< .05) contrast indicates that one group improved more rapidly than the other. The magnitude of this effect will be examined through the standardized mean difference effect size of the slope contrast (i.e., difference between the two conditions’ slopes divided by the square root of the overall slope variance), with clinical significance examined in terms of model-implied outcomes at 6, 12, and 18 months within each group. To complement these primary symptom trajectory outcomes, we will also examine change in total number of diagnoses on the modified MINI-KID-P at post-treatment using generalized linear models, controlling for baseline diagnoses.

### Aim 2

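### Research participation, not only study treatment, may be ended when a youth's risk rises, so outcome data can stop for a reason tied to the outcome

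*Protocol article*

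**What the plan says.** The rule stands in the protocol article under Participants, Exclusion Criteria. Two conditions must be met: the youth's risk of suicidal or homicidal behaviour has increased during participation, and the clinic and its clinicians have decided that a higher level of care is needed. In that case "research participation may be ended to ensure access to an appropriate level of care". The article does not say that outcome assessments continue afterwards.

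Planned Analyses covers the gaps that follow: "Missing data will be accommodated using full information maximum likelihood estimation or multiple imputation". The same section says that missing-data characteristics will be examined and models adjusted.

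Table 1 and its notes set the schedule. The CBCL and YSR are collected at about 0, 3, 6, 9, 12 and 18 months. The BFS and the Top Problems Assessment are collected weekly during therapy and then on the same quarterly schedule. That schedule runs from baseline whatever the length of treatment, so a youth who is discharged stays in follow-up. The Measures section says that youth and caregiver measures are completed by online survey or telephone.

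Sample Size and Power states "we anticipate an attrition/data loss rate of 15% will occur between allocation and analyses".

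**The concern.** The event that can end data collection is a serious clinical worsening, and clinical worsening is what the outcomes measure. A youth who is discharged stays on the quarterly schedule, while a youth who is stepped up to more intensive care may leave it. If the worsening falls between two assessments, the last recorded scores predate it. A likelihood model or an imputation under missing-at-random then projects that youth's later course from data that look better than the truth.

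Two features make an imbalance between arms possible. First, clinicians take part in the decision that triggers the rule, and they know their condition; only the assessors are described as naive to it. Second, FIRST clinicians receive weekly symptom feedback and expert consultation, and usual-care clinicians receive neither from the study. Detection of worsening and step-up in care could therefore differ by arm. At stake is the slope contrast that carries Aim 1, and the model-implied outcomes at 12 and 18 months.

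**Working it through.** **The plan's own figure.** The minimum of 180 youths, inflated for 15% loss, is 180 / (1 - 0.15) = 211.8, rounded up to 212. The target reproduces, so there is no arithmetic error. The article does not say what share of the 15% this rule would cause.

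**When is the estimate biased?** Likelihood estimation and multiple imputation, as ordinarily applied, need the chance of stopping to depend only on recorded data. The outcomes differ in how well that is met:

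- BFS and Top Problems during therapy: weekly, so a build-up to a crisis has a fair chance of being recorded.
- BFS and Top Problems after therapy: quarterly only.
- CBCL and YSR throughout: three months between assessments, and six months between months 12 and 18. A crisis inside an interval can end participation before any score shows it.

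**Illustration by simulation.** The set-up was 6,000 youths, visits at 0, 3, 6, 9, 12 and 18 months, random intercepts and slopes each with SD 1 (time scaled so that 18 months = 1), residual SD 0.5, a true slope contrast of -0.50 (FIRST better), a maximum-likelihood mixed model, and no clinician clustering. The stopping rules and rates are assumed.

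| Stopping rule | Lost by month 18, UC / FIRST | Estimated contrast |
|---|---|---|
| None | 0 / 0 | -0.50 |
| After a worsening that was recorded, both arms | 22% / 14% | -0.50 |
| At a worsening that was not recorded, both arms | 25% / 15% | -0.39 |
| The 15% with the worst true slopes, lost after month 3, both arms | 21% / 9% | -0.33 |
| Unrecorded worsening, UC only | 25% / 0 | -0.24 |
| Worst true slopes, UC only | 21% / 0 | -0.17 |

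The second row shows no bias. The rows below it do, and all shrink the contrast towards zero. Their losses are far heavier than a narrow safety rule is likely to cause, so they show the mechanism and direction, not the expected size.

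**A smaller-scale calculation.** If a proportion p of an arm is lost this way, and the unseen 18-month outcome is k SD worse than the model predicts, that arm's mean looks p × k too good. With the same k in both arms, the contrast is off by (p_UC - p_FIRST) × k. The documents give none of these inputs. Assumed ranges are p_UC 5-10%, p_FIRST 2-5% and k 1-1.5 SD:

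| p_UC | p_FIRST | Difference | k = 1.0 | k = 1.5 |
|---|---|---|---|---|
| 0.05 | 0.05 | 0.00 | 0.00 | 0.00 |
| 0.05 | 0.02 | 0.03 | 0.03 | 0.045 |
| 0.10 | 0.05 | 0.05 | 0.05 | 0.075 |
| 0.10 | 0.02 | 0.08 | 0.08 | 0.12 |

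The range is 0 to 0.12 SD. This is a difference in 18-month means. The design effect of 0.50 is a slope difference standardised by slope variance, so the two should not be divided into each other.

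**The case against.** The rule is a narrow safety provision. It needs raised suicidal or homicidal risk and a judgement that more intensive care is required, and even then it is permissive. Youths with current suicide risk are excluded at entry, and no frequency is given. Worsening recorded before the ending stays in the likelihood, and the weekly measures are themselves primary outcomes. The missing-at-random assumption is inferred from the methods named, not stated, and sensitivity analyses may sit in an analysis plan that is not shown. If usual care loses more of its worst cases, the error is conservative for FIRST.

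Most of this stands. It limits the size of the problem and rules out calling bias certain. It does not remove the point, because an analysis plan can model missing outcomes but cannot recover data that a protocol rule stopped collecting. Nor is the direction assured: by the same formula, if FIRST lost more youths this way, the sign would reverse and favour FIRST.

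A reader might also infer that 32 randomised youths (212 - 180) are left out of the primary analysis, because the Aim 1 model is written with 180 participants. The documents do not support that. Sample Size and Power derives 180 as the planning minimum ("180 youth participants was required to achieve adequate power (1-β = 0.80) to detect an effect size of 0.50"), and Aim 1 repeats it beside the 24 clinicians from the same calculation. Nothing excludes a randomised youth. Eligibility requires a caregiver CBCL, and every youth with data can enter a likelihood model.

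**Conclusion.** The point holds as a weakness of a stated rule. Outcome collection can stop because a youth has worsened, and the named missing-data methods deal with that only where the worsening has already been recorded. The quarterly CBCL and YSR are the most exposed. The size is unknown because the frequency of such endings is not given. Under the assumed inputs, the bias in the 18-month contrast is 0 to 0.12 SD. It runs against FIRST if usual care loses more of its worst cases, and it vanishes if losses and shortfalls are equal in the two arms. Two stronger readings fail: that any youth who deteriorates is removed, and that both arms must look better than they were. The trigger is narrower than general deterioration, and bias is not automatic. The change is worth making because it is cheap and uses assessments already on the schedule.

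**What to change.** Separate leaving study treatment from leaving outcome follow-up. State that, after a step-up in care, the scheduled quarterly caregiver and youth surveys continue by the existing online or telephone route unless consent or assent is withdrawn. The care decision stays with the clinic and is not affected. Record the date and reason of every ended participation, so that endings under this rule can be counted by arm.

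As a supporting analysis, add a delta-adjusted sensitivity analysis for youths whose participation ended for this reason: make their unseen outcomes progressively worse than predicted, allow the shift to differ by arm, and report where the Aim 1 conclusion changes.

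The cost is minor protocol and consent wording with IRB review, and a few more survey payments. Some families will decline. Youth recruitment began in September 2021, so follow-up already ended cannot be recovered; for those youths only the sensitivity analysis helps.
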